### Study design

This is a multi-center, two-group, parallel, RCT to compare the effects of two 12-week interventions: Internet-based Cognitive Behavioral Treatment (iCBT) plus treatment as usual (TAU) or TAU only, designed to demonstrate statistical superiority. The proposed flow of participants through the trial is shown in Fig. 2. Assessments and biomarkers are completed by all participants at baseline (pre randomization) and post treatment at week 13 and week 52.

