#### Outcome measures

Primary outcome is change in alcohol consumption in mean grams per week and mean number of days with heavy drinking (that is > 4/5 drinks for women and men) the last 30 days from baseline to 12 and 52 weeks post inclusion. A drink contains 12 g of alcohol.

For all secondary outcomes mean change from baseline to 12 and 52 weeks post inclusion applies; hazardous drinking and severity of dependence, health-related quality of life, symptoms of depression and anxiety and difference in biomarker levels of heavy drinking and liver pathology.

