### Statistical analyses and sample size calculations

Baseline participant characteristics stratified by treatment group will be presented. Group differences will be tested using a *t* test for continuous variables and chi-square tests for categorical outcomes. Multiple imputation will be used to replace missing internal values where appropriate. Within-group changes in the primary outcome (alcohol consumption) and secondary outcomes (*ICD-10* criteria, AUDIT scores, depression, anxiety, EQ-5D-5 L and biomarkers) at 12 and 52 weeks will be analyzed according to the intention-to-treat principle, using linear mixed models and Poisson regression where appropriate. The models will further be adjusted for baseline covariates and treatment adherence. Per-protocol analyses will also be presented. All tests will be two-sided and *p* values of less than 0.05 considered statistically significant.

The study is designed to demonstrate statistical superiority. An effect-size of 0.61 has been shown in previous Internet studies on high consumers in the general population [25]. Due to a lack of studies on alcohol-dependent patients, our estimate is based on a more conservative effect-size of 0.4, which requires the estimated sample size of 100 participants in each arm to get a power of 80% and a statistically significance 0.05 when using a *t* test. Given an estimated dropout in iCBT of 30%, 260 participants are included in the study [26].

No interim analyses are planned.

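### The only stated baseline adjustment is bundled with treatment adherence, so the plan describes no baseline-adjusted comparison of the arms that is free of a post-randomisation variable

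*Protocol article*

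**What the plan says.** Under Outcome measures, the Protocol article states: "Primary outcome is change in alcohol consumption in mean grams per week and mean number of days with heavy drinking", over the last 30 days, from baseline to the two follow-ups. Under Study design, all participants are assessed "at baseline (pre randomization) and post treatment at week 13 and week 52", so a pre-randomisation value of both primary measures is available.

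Under Statistical analyses and sample size calculations, the quantities to be analysed are "Within-group changes in the primary outcome (alcohol consumption) and secondary outcomes", and these "will be analyzed according to the intention-to-treat principle, using linear mixed models and Poisson regression where appropriate". The adjustment sentence then reads: "The models will further be adjusted for baseline covariates and treatment adherence". The covariates are not listed. Testing is two-sided at 0.05. The sample size is 100 per arm for an effect size of 0.4, chosen "to get a power of 80% and a statistically significance 0.05 when using a *t* test", and is raised to 260 in total for dropout.

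Under Program engagement, engagement is counted from assignments accessed and tasks completed, and its association with outcome is to be explored.

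**The concern.** The adjustment sentence joins two variables of different kinds. A baseline value is fixed before randomisation. Adjusting for it leaves the randomised comparison intact and usually sharpens it. Adherence is observed after randomisation and can be affected by the assigned arm. Conditioning on it means the result is no longer the plain intention-to-treat contrast. If adherence is taken from the engagement counts, the treatment-as-usual arm has no equivalent measure.

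Because the two sit in one step, a reader cannot find a model that has the first without the second. At stake are the clarity of the main comparison and, for grams per week, precision that the data already collected could supply.

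**Working it through.** **1. The two readings of the adjustment sentence.**

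- *Further* as a second model: the first model is free of adherence but has no stated baseline adjustment, and the second has both.
- *Further* as *also*: every model carries adherence.

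On neither reading is a model described that adjusts for baseline and leaves adherence out.

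**2. The plan's own sample size.** Inputs from the analysis section: d = 0.4, two-sided alpha 0.05, power 80%, t test. The required size is 99.08 per arm, which rounds up to 100. Power at 100 per arm is 80.4%. The stated figure reproduces.

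**3. Variance with and without baseline adjustment (grams per week).** Let rho be the correlation between baseline and follow-up, with the same variance (set to 1) at both. The documents give neither quantity, so equal variance is an assumption and rho is shown over a range.

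- Change score: 2(1 − rho)
- Adjusted for baseline: 1 − rho²
- Ratio, adjusted to change: (1 − rho²) / [2(1 − rho)] = (1 + rho)/2

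| rho | change | adjusted | ratio |
|---|---|---|---|
| 0.3 | 1.40 | 0.91 | 0.65 |
| 0.5 | 1.00 | 0.75 | 0.75 |
| 0.7 | 0.60 | 0.51 | 0.85 |

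**4. Power at 100 per arm.** The protocol does not say which SD the 0.4 refers to, so both are shown. On the change SD, the adjusted effect size is 0.4/√((1 + rho)/2); for example, at rho 0.5 it is 0.4/√0.75 = 0.462. On the single-visit SD, 0.4 is divided by the square root of the variance in step 3.

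| rho | d on change SD: change → adjusted | d on single-visit SD: change → adjusted |
|---|---|---|
| 0.3 | 80.4% → 93.7% | 66.2% → 83.9% |
| 0.5 | 80.4% → 90.2% | 80.4% → 90.2% |
| 0.7 | 80.4% → 86.3% | 95.3% → 97.6% |

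**5. Does naming a mixed model settle it?** In 150 simulated trials (100 per arm, three visits, rho 0.5, complete data), a mixed model with free baseline means in each arm gave the change-score estimate exactly: empirical SE 0.143, correlation with chance baseline imbalance −0.49. A mixed model with a common baseline mean gave SE 0.125 and a correlation near zero, matching analysis of covariance (SE 0.125). So the answer depends on a detail that the words *linear mixed models* do not fix.

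**6. Is chance imbalance an extra cost?** The change-score variance splits as 2(1 − rho) = (1 − rho²) + (1 − rho)². At rho 0.5 this is 1.00 = 0.75 + 0.25. The second term is the baseline imbalance carried into the estimate, and it is the whole of the excess in step 3. The power loss and the imbalance are therefore one cost.

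**The case against.** The strongest reply is that the efficiency loss belongs to a model the protocol never states. It names linear mixed models, not a change-score test. Defining the outcome as change does not prescribe an unadjusted analysis. A mixed model with a common baseline mean already recovers the precision, and if *further* means *also*, baseline may be in the main model. A condensed article may leave parameterisation and the covariate list to the full protocol or analysis plan. All of this stands, and it makes the power figures conditional. It does not answer the bundling: the article does state an adjustment set, and that set includes adherence.

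A reader might infer several stronger things that the document does not support:

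- *That the trial is underpowered.* With d on the change SD, the planned 80% is kept and adjustment only adds to it. With d on the single-visit SD, change-score power falls below plan only if rho is under 0.5, and at rho 0.7 the gain is about 2 points. Sizing on an unadjusted t test is conventional.
- *That chance imbalance biases the result.* Over repeated randomisations it does not. It is part of the sampling variance, as step 6 shows.
- *That entry through a minimum AUDIT score makes this worse.* The threshold is applied before randomisation, so any regression to the mean affects both arms alike.
- *That the same loss applies to both primary measures.* Heavy-drinking days is a count and presumably the Poisson outcome, for which the ratio (1 + rho)/2 does not hold.

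**Conclusion.** The point holds as a defect in the stated adjustment step. On either reading of the sentence, the plan describes no baseline-adjusted comparison free of adherence, and the outcome's own baseline value is not named.

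The loss of precision is conditional. It arises for grams per week if the adherence-free model is a change score or a mixed model with free baseline means. Under equal variances and 100 per arm, the forgone power at rho 0.3, 0.5 and 0.7 is then about 13, 10 and 6 points with d on the change SD, or about 18, 10 and 2 points with d on the single-visit SD. The document does not establish that such a model is intended. Confidence is therefore high on the bundling and moderate on the size of its effect.

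**What to change.** Replace the adjustment sentence for the primary analysis with one that states:

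- The primary between-group intention-to-treat model for each primary measure includes that measure's own baseline value as a covariate, with weeks 13 and 52 as the repeated outcomes and group-by-time terms. A longitudinal model with a baseline mean common to both arms is an acceptable alternative.
- If heavy-drinking days is analysed as a count, log(baseline + 1) is the covariate.
- Adherence is excluded from this model and moves to a separate exploratory analysis, alongside the engagement analysis already planned.

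The cost is a sentence or two in the protocol or analysis plan, fixed before the allocation codes are released. No new data, participants or visits are needed. For the linear model, the randomised mean difference being estimated is unchanged.

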#### Randomization, treatment allocation and blinding

The randomization was done in blocks of 20 according to a fully automated and concealed procedure in the online platform that was programmed in the content management system Drupal (drupal.org) by the fourth author. The research nurse randomizes all eligible participants via the online platform by activating a link that only she has access to. Type of treatment (iCBT + TAU vs TAU) is not blinded neither for the participants nor the research nurse. Hence, unblinding of participants and the research nurse will not be necessary during the trial. Responsible researchers as well as data analysts will not have access to the codes concerning which experimental condition the participants participate in until after completion of analysis of the primary outcome measure. Hence, the risk of bias in the interpretation of the study’s result is minimal.

The participants are informed by the research nurse about their group allocation and are scheduled for a blood test for biomarkers and an appointment with the GP at the PC clinic, ideally within 2–3 weeks. The GPs give all participants feedback on the assessment and biomarkers and design a treatment plan based on current routines at the PC clinic. For those randomized to iCBT, the Internet program will be made available the following Monday after randomization.

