#### Internet-based Cognitive Behavioral Therapy

The intervention group will be given iCBT in addition to TAU. The iCBT program is based on the self-help material used in previous studies on the Internet [18, 21] and in primary care [13]. iCBT includes five elements: (1) Motivation to cut down or stop drinking, (2) Goal-setting for alcohol consumption per occasion and weekly consumption and self-control strategies; for example, not to have alcohol at home and strategies to drink more slowly, (3) Chart risk situations and conduct behavior analysis on occasions with too much alcohol, (4) Plan alternative activities to drinking alcohol and (5) Relapse prevention and crisis plan and mapping of life situations or stressors that can lead to relapse. The intervention is open-ended, meaning that participants can log on as often and for as long as they want.

For each assignment an informational text is provided and a home assignment is included. iCBT is an extended self-help intervention with automated feedback where participants repeatedly are reminded to start and complete every assignment.

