#### Program engagement

Program engagement will be measured by automatic data collection on number of assignments accessed, tasks completed. Association between program engagement metrics and treatment outcomes will be explored.

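### The intention-to-treat models are to be adjusted for treatment adherence, a post-randomisation variable, so the adjusted group coefficient does not estimate the effect of being randomised to iCBT

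*Protocol article*

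**What the plan says.** Under Statistical analyses and sample size calculations, the protocol says that the primary outcome and the listed secondary outcomes at 12 and 52 weeks "will be analyzed according to the intention-to-treat principle, using linear mixed models and Poisson regression where appropriate". The next sentence reads "The models will further be adjusted for baseline covariates and treatment adherence". Two sentences that follow or stand close by cover neighbouring analyses. The same section adds "Per-protocol analyses will also be presented", and the Program engagement section says "Association between program engagement metrics and treatment outcomes will be explored". The adherence adjustment is listed in addition to both and carries no sensitivity or exploratory label.

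The statistical section does not define treatment adherence. The nearest description is in Program engagement: "Program engagement will be measured by automatic data collection on number of assignments accessed, tasks completed". The treatment section states that "The intervention group will be given iCBT in addition to TAU", so those data can arise in one arm only. The section on randomisation and blinding says that researchers and analysts "will not have access to the codes concerning which experimental condition the participants participate in" until the primary outcome has been analysed.

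**The concern.** The sentence treats adherence as if it were the same kind of variable as a baseline covariate. Baseline covariates are fixed before allocation, so adjusting for them leaves the randomised comparison intact. Adherence is observed afterwards and can depend both on the arm and on the participant's prognosis. Conditioning on it removes whatever part of the benefit works through using the treatment. It also lets differences between users and non-users into the group coefficient.

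The hypothesis is that adding iCBT to TAU reduces drinking more than TAU only. That is a question about the randomised contrast. A coefficient from the adherence-adjusted model, reported under the intention-to-treat label, could hide a real benefit, show the opposite sign, or show a difference where none exists. Because the text does not say which model decides superiority, it also leaves room to choose after both results are seen.

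**Working it through.** **Reading of the text.** The subject of the adjustment sentence can only be the intention-to-treat models named just before it. The protocol words these as within-group changes, but the hypothesis and the superiority aim need the between-group coefficient, so that is what is examined here.

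**The plan's own figure.** Inputs from the sample-size paragraph: effect size 0.4, two-sided 0.05, power 80%. n per arm = 2(1.96 + 0.84)²/0.4² = 98 to 99 by the normal formula and 99.1 by the t test. The stated 100 is reproduced, with power 0.804. The numbers below use 100 per arm and a true effect of 0.40 SD, with positive values meaning benefit from iCBT.

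**What the adjusted coefficient is, if adherence A is 0 throughout TAU.** The TAU mean fixes the intercept, so the adherence slope b_A comes from the iCBT arm alone:

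b_group = (mean iCBT − mean TAU) − b_A × mean(A in iCBT)

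This equals the randomised effect only if b_A is zero. Apart from an accidental cancellation, that requires adherence to be unrelated both to prognosis and to the size of the treatment effect.

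**Assumptions (none is given in the documents).** A is uniform on 0-1 in iCBT (mean 0.5, variance 1/12). The correlation ρ between prognosis and the normal score underlying A is 0, 0.2 or 0.4.
- Slope from prognosis: [ρ/(2√π)]/(1/12) = 3.385ρ. Times the mean of 0.5, it shifts the coefficient by −1.69ρ, which is −0.34 at 0.2 and −0.68 at 0.4.
- Slope from treatment when the effect works entirely through use: 0.8. Times 0.5, it removes a further 0.40.

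Ordinary least squares in 4000 simulated trials per scenario agrees with these formulas:

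| Scenario | ρ | Unadjusted coefficient (rejection rate) | Adherence-adjusted coefficient (rejection rate) |
|---|---|---|---|
| Effect entirely through use | 0 | 0.40 (79%) | 0.00 (5%) |
| | 0.2 | 0.39 (76%) | −0.34 (34%) |
| | 0.4 | 0.40 (76%) | −0.68 (89%) |
| Effect unrelated to use | 0 | 0.40 (80%) | 0.40 (43%) |
| | 0.2 | 0.40 (80%) | 0.06 (6%) |
| | 0.4 | 0.40 (80%) | −0.28 (24%) |
| No effect | 0 | 0.00 (5%) | 0.00 (5%) |
| | 0.2 | 0.00 (5%) | −0.34 (33%) |
| | 0.4 | 0.00 (5%) | −0.67 (88%) |

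**Standard error.** With equal arms and A = 0 in TAU, the squared correlation of group and adherence is μ²/(μ² + 2σ²), where μ and σ are the mean and SD of A in iCBT. The standard error is therefore multiplied by √(1 + μ²/(2σ²)).
- Continuous uniform: √(1 + 0.25/(2/12)) = √2.5 = 1.58. The simulation gives 0.141 rising to 0.225.
- Uniform over 0 to 5 modules (μ = 2.5, σ² = 35/12): √(1 + 6.25/5.833) = 1.44.
- An increase of 35% to 60% corresponds to μ/σ between √(2(1.35² − 1)) = 1.28 and √(2(1.60² − 1)) = 1.77.

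**If adherence were instead measured in both arms.** The zero-use algebra would not apply. The coefficient would compare the arms at equal adherence, which is still a post-randomisation quantity and not the randomised effect. These inputs do not give the size of that error.

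**The case against.** Four points on the other side deserve weight.

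1. *The adjusted model may be a second step.* The adverb in the adjustment sentence can mean that an unadjusted intention-to-treat model comes first. A reader might infer from the sentence that the adherence-adjusted result is the main one, so that the trial cannot test its hypothesis. The text does not establish that, because on the second-step reading the randomised estimate is still produced. What remains is that the adjusted coefficient is wrong for its stated purpose on either reading, and that no model is named as decisive.

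2. *Adherence is undefined.* Both arms receive TAU with a GP appointment and a treatment plan, so adherence could be a two-arm measure, and programme engagement has its own section. This stands: the one-arm definition is inferred. The post-randomisation objection survives it, but the zero-use contrast, the standard-error figures and the table do not.

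3. *Blinding.* A reader might infer a contradiction with the blinding section, because a variable present in one arm only reveals the arm. The documents do not show one. Codes are withheld only until the primary outcome has been analysed, so a conflict needs both one-arm adherence and its use in the primary-outcome model. It is a conditional risk.

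4. *The sizes are illustrative.* They rest on an assumed distribution, assumed correlations and a cross-sectional linear model, whereas the plan uses mixed and Poisson models with two follow-ups. The negative shifts assume that users have the better prognosis. With the opposite correlation the same algebra gives a false benefit. This is accepted. The sizes show what can happen, and the argument does not depend on them.

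**Conclusion.** The point holds. The protocol states a rule under which intention-to-treat models include a post-randomisation variable that allocation can affect, and the resulting group coefficient does not estimate the effect of randomisation to iCBT. That needs no assumption about how adherence is defined or whether an unadjusted model comes first. No separate analysis absorbs the problem, since the per-protocol and engagement analyses are listed in their own right.

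The size depends on two assumptions: that adherence means programme use, and how that use is distributed and related to prognosis. Under those examined, a true 0.40 SD effect can appear as anything from 0.40 to −0.68. A null effect can be rejected in 33% to 88% of trials at ρ of 0.2 to 0.4. Where there is no bias, power still falls from 80% to 43%. The claims that the trial's main result is unusable, or that the blinding rule is broken, go further than the documents allow.

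**What to change.** In the adjustment sentence, delete the last three words. State that the intention-to-treat models adjust only for pre-randomisation covariates, including the baseline value of the outcome, and that this model tests superiority.

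Move adherence to the exploratory engagement analysis already planned, or to another clearly labelled supplementary analysis. A complier-average analysis using randomisation as the instrument is one example and not a requirement. Define adherence there, run that analysis after the blinded primary analysis is complete, and keep platform-use variables out of the dataset the blinded analysts receive.

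The cost is one or two sentences of wording. No new data are needed, and the 100 per arm calculation is unaffected because it assumed a plain two-group comparison.

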**Methods:**

This is a two-group, parallel, randomized controlled trial (RCT). The aim is to study whether an Internet-based Cognitive Behavioral Treatment (iCBT) when added to treatment as usual (TAU) is more effective than TAU only for alcohol dependence in PC. Two hundred and sixty adults with alcohol dependence will be included. Participants are randomized to iCBT and TAU or TAU only. The primary study outcome is alcohol consumption in grams per week and heavy-drinking days. Secondary outcomes include alcohol-related problem severity, number of diagnostic criteria for alcohol dependence, depression and anxiety symptoms, health-related quality of life and biochemical markers for high consumption and liver pathology. Data will be analyzed using mixed-effect models.

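### The 260 to be randomised is 200 × 1.3, not 200 / 0.7: if the 30% is loss to follow-up, the iCBT arm ends at 91 rather than 100, and the 80% power then depends on a TAU loss rate that is not stated

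*Protocol article*

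**What the plan says.** The section *Statistical analyses and sample size calculations* of the protocol article builds the sample size in two steps.

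- **Base size.** The authors explain that "our estimate is based on a more conservative effect-size of 0.4". From this they derive a need for 100 per arm, with power set at 80% for a t test at the 0.05 level. Earlier in the section they specify that "All tests will be two-sided".
- **Inflation.** The total then follows in one sentence: "Given an estimated dropout in iCBT of 30%, 260 participants are included in the study".

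The abstract repeats the total: "Two hundred and sixty adults with alcohol dependence will be included". The section gives no loss rate for the TAU arm and does not say whether dropout means leaving follow-up or leaving the programme. The analysis it plans is by intention to treat, using linear mixed models, Poisson regression where suitable, and some multiple imputation. The power statement rests on the t test alone.

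**The concern.** To keep a required number after a proportion *p* is lost, that number is divided by (1 − *p*). Multiplying by (1 + *p*) gives too few, and the gap grows with *p*. At 30% it is no longer a rounding matter. The total of 260 is exactly what the multiplication gives, so the randomised number does not follow from the inputs printed beside it.

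What is at stake is how the result is read. If the trial finds no difference, readers will use the stated 80% power at 0.4 to judge what was ruled out. On the loss-to-follow-up reading, that figure holds only under a TAU retention assumption that the text never makes.

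**Working it through.** **Inputs, all from the sample-size section unless noted**

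- Standardised effect d = 0.4; two-sided alpha 0.05; power 80%; two-sample t test.
- Required size 100 per arm, 200 in all.
- Dropout 30%, stated for iCBT; none stated for TAU.
- Total randomised 260.
- Allocation 1:1, hence 130 per arm. This is an assumption: the ratio is not stated, but the required size is given as equal arms and randomisation is in blocks of 20.

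**Step 1: reproduce the base size.** The normal approximation is n = 2(1.960 + 0.842)² / 0.4² = 98.1, so 99 per arm. The exact t test needs 99.08, so 100 per arm. Power at 100 per arm is 80.4%. The stated 100 is right.

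**Step 2: reproduce the total.**

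| Rule | Calculation | Total |
|---|---|---|
| Multiply both arms by 1.3 | 200 × 1.3 | 260 |
| Divide both arms by 0.7 | 200 / 0.7 = 285.7 | 286 (143 per arm) |
| Divide the iCBT arm only | 100 / 0.7 + 100 = 242.9 | 243 |

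Of these, only the first gives the printed figure. It is 286 − 260 = 26 short of the number that keeps 100 per arm after 30% loss in both.

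**Step 3: what remains.** 130 × 0.7 = 91 in an arm that loses 30%. An arm of 130 keeps 100 only if its loss is at most 1 − 100/130 = 23.1%.

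**Step 4: power if the 30% is loss to follow-up.** The noncentrality is d × √(n₁n₂ / (n₁ + n₂)). For 91 against 91 it is 0.4 × √45.5 = 2.70. Power from the noncentral t, two-sided 0.05, with iCBT at 91:

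| TAU loss | TAU n | Power at d = 0.4 |
|---|---|---|
| 0% | 130 | 83.0% |
| 10% | 117 | 81.3% |
| 16% | 109.2 | 80.1% |
| 20% | 104 | 79.2% |
| 30% | 91 | 76.5% |

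Break-even for 80% is a TAU n of 108.7, which is a loss of 1 − 108.7/130 = 16.4%. The normal approximation for 91 against 91 is 77.0%. At 91 per arm, 80% power is reached at d = 0.418.

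**Step 5: if the 30% is stopping the programme.** With all 260 followed, 130 against 130 are analysed. At d = 0.4 that gives 89.5% power, provided 0.4 already allows for people who stop. No inflation for missing data belongs in that calculation.

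**The case against.** **The 30% is stated for iCBT only.** Taken literally, with no TAU loss, power is 83.0%, and it stays at or above 80% up to about 16% TAU loss. This stands. A reader might infer that the 80% needs almost complete TAU follow-up, or that the trial is underpowered as it is. The document supports neither, because 76.5% needs a 30% TAU loss that it does not state. What the objection does not rescue is the derivation: iCBT still ends at 91, and inflating that arm alone gives 243, not 260.

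**Dropout may mean leaving the programme.** The wording attaches dropout to iCBT, *Study design* has all participants assessed at weeks 13 and 52, and *Baseline and follow-up assessments* describes active reminders. On this reading 130 per arm are analysed. A reader might infer that 100 per arm is missed whatever dropout means; that fails here. A reader might also go the other way and infer heavy dilution: if the 30% who stop gain nothing, and 0.4 is a full-adherence effect, the effect falls to 0.7 × 0.4 = 0.28 and power to about 61%. The document supports neither assumption. If 0.4 already reflects non-adherence, power is 89.5%. The range of 61% to 89.5% shows only that the term needs defining.

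**The planned analysis is not a completers' t test.** Mixed models use partial data, and adjustment for the baseline outcome can recover power. If 0.4 is in raw standard-deviation units, 91 per arm gives 78.2%, 80.3%, 83.4% and 87.3% for assumed baseline–outcome correlations of 0.2, 0.3, 0.4 and 0.5. This softens the consequence. But the document gives no correlation and rests its power statement on the t test.

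**Nothing is promised.** The text never says that 100 analysable per arm is secured. That is so: it states a requirement and then a total, and the fault is that the total does not meet the requirement at the stated loss.

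**Conclusion.** The point holds as an arithmetic error of modest size. The base of 100 per arm is correct. The total of 260 comes from multiplying by 1.3 and falls 26 short of the 286 that would keep 100 per arm after 30% loss in both.

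If the 30% is loss to follow-up and allocation is 1:1, the iCBT arm ends at 91, and power at 0.4 lies between 83.0% and 76.5% as TAU loss runs from 0 to 30%. The largest shortfall over that range is 80 − 76.5 = 3.5 points, and the effect detectable with 80% power moves from 0.40 to about 0.42. If everyone is followed, the shortfall in numbers does not arise, but then the stated reason for enrolling 260 is not the right one.

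This does not threaten the design, the analysis or the conduct of the trial. It is a printed figure that does not follow from its own inputs. It should be corrected, but it is not a must-fix defect.

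**What to change.** Keep 260 and restate what it delivers:

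1. Say that 260 randomised 1:1, with 30% loss to follow-up in both arms, gives 91 analysable per arm and about 76–77% power at an effect size of 0.4, or 80% at about 0.42.
2. State the loss assumed in TAU. If it is lower than in iCBT, quote the matching power; up to about 16% TAU loss, the 80% can stay.
3. Say whether the 30% means loss to follow-up or stopping iCBT. If it means stopping iCBT with follow-up continued, remove it as the reason for the inflation and say whether 0.4 already allows for non-adherence.

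No extra participants are needed and the abstract's total is unchanged. The cost is a slightly less favourable stated power if loss is expected to be similar in both arms.
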